The criteria for eligibility will be confirmed on the day of infusion. The cell product will be obtained from the BMDI Cord Blood Bank a day before the transfusion. CBU released from the Cord Blood Bank for this study will have undergone all pre-release testing as routinely performed for release for bone marrow transplant, and have met compliance with the AusCord Quality & Release Criteria. The CBU will be released under “Exceptional Release” and the TGA notified as the bank is not licensed for the release of unrelated allogeneic non-homologous use. The product will be thawed at Monash Health Translation Precinct's Cell Therapy and Regenerative Medicine Platform. After thawing, washing of cells (to remove DMSO, a cryopreservant) will be undertaken using Dextran-Albumin and resuspended in 4% albumin as per standard clinical practice. Cell viability (>70% viable CD34+ cells, in accordance with the AusCord Quality & Release Criteria.) will be determined before administration. UCBCs will be administered intravenously (through a peripheral intravenous catheter) within one hour of thaw at a dose of 50 million (as available in aliquot) viable TNCs/ kg body weight. The exact dose will depend on the number of viable TNCs available in the final cell product. The volume of cell infusion(s) will be 10 mL/kg, and cell infusion will occur over one hour undertaken in the neonatal unit or the clinical trials facility of Monash Children's Hospital. The custody of care of the product will be transferred from BMDI Cord Blood Bank to the shipper to Monash Health Translation Precinct's Cell Therapy and Regenerative Medicine Platform to the clinical team using appropriate standard operating procedures.

- 1. ***Statistical analysis***

Descriptive statistics will be used to report demographics and outcomes. The categorical variables will be described as frequency and percentage and continuous variables as median (interquartile range) and mean (standard deviation), depending on the normality of the data, which will be determined by the Shapiro-Wilk test. The data will be analysed using STATA Version 17.0 (StataCorp LLC, College Station, TX, USA). Paired t-tests or Wilcoxon signed-rank tests will be performed to compare the laboratory parameters before and after infusion.

- 1. **Safety monitoring and reporting**
     1. Monitoring **(Figure 1 and Table 1):**
        1. The following will be monitored during and within 48 hours of infusion.
     - During infusion

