       - Local site reaction (erythema, oedema, extravasation at site of peripheral intravenous catheter site).
       - Any sustained change of 30% or more from baseline in vital signs (HR, RR, BP, SpO2, Temperature).
     - Within the first 48 hours of infusion
       - Any event requiring cardiopulmonary resuscitation.
       - Escalation of respiratory support (intubation of an infant receiving non-invasive respiratory support; or change to high-frequency oscillatory ventilation in an infant receiving conventional ventilation at the time of UCBC infusion).
       - Fluid bolus or initiation/escalation of inotropic support.
       1. Infants will also be monitored clinically for infection within 48 hours of UCBC infusion. Appropriate tests will be performed to diagnose infection (culture-proven bacterial, fungal, viral infection, culture-negative, clinically suspected infection).
       2. Infants will be monitored for features of acute GVHD in the first three months after cell infusion, which includes
          1. Skin involvement: Any erythematous rash with or without skin peeling
          2. Gastrointestinal involvement: vomiting and diarrhoea
          3. Liver involvement: jaundice, conjugated hyperbilirubinemia, and abnormal liver function tests (LFTs).
       3. Physical examinations will be performed before the infusion. Further examinations will be performed at 1, 2, 3, 6, 9, 12, 18 and 24 months post-infusion. In the physical examinations, infants will be evaluated for features of chronic GVHD, such as

Skin involvement: rash, dryness, itching, thickening, change of colour, and temperature intolerance

Nail involvement: nail loss, brittle nails, abnormal texture

Hair involvement: loss of body or scalp hair, grey hair

Mouth involvement: dryness, sensitivity, ulcers, gum disease, tooth decay

Gastrointestinal and liver involvement: loss of appetite, nausea, vomiting, diarrhoea, abdominal distension, abdominal pain, jaundice, abnormal LFTs

Lung involvement: persistent cough, wheezing, breathing difficulties

Musculoskeletal involvement: muscle weakness and cramps, joint stiffness

Genitalia involvement: dryness, ulceration, itching, scarring, narrowing of orifices

- - - 1. The following neurodevelopmental assessments will be performed.

At term-equivalent age: General movements assessment and Hammersmith neonatal neurological examination

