**Respiratory/ Cardiovascular**

| **Gas** | **pH** | **pCO2** | | **pO2** | **BE** | **HCO3** | **Lactate** | **OI** | **RSS** |
| --- | --- | --- | --- | --- | --- | --- | --- | --- | --- |
| **-1h** |  |  | |  |  |  |  |  |  |
| **Settings** |  | | | **MAP** |  | **FiO2** |  |  | |
| **Acceptable** |  | |  |  |  |  |  |  |  |
| **1h** |  |  | |  |  |  |  |  |  |
| **Settings** |  | | | **MAP** |  | **FiO2** |  |  | |
| **6h** |  |  | |  |  |  |  |  |  |
| **Settings** |  | | | **MAP** |  | **FiO2** |  |  |  |
| **Cessation of acceptable limits for gas** | | | | | | | | | |
| **12h** |  |  | |  |  |  |  |  |  |
| **Settings** |  | | | **MAP** |  | **FiO2** |  |  |  |
| **24h** |  |  | |  |  |  |  |  |  |
| **Settings** |  | | | **MAP** |  | **FiO2** |  |  | |
| **48 h** |  |  | |  |  |  |  |  |  |
| **Settings** |  | | | **MAP** |  | **FiO2** |  |  |  |

| **Time**  **(hrs)** | **-2** | **-1.75** | **-1.5** | **-1.25** | **-1** | **-0.75** | **-0.5** | **-0.25** | **0** | **Accept-able** |
| --- | --- | --- | --- | --- | --- | --- | --- | --- | --- | --- |
| **BP** |  |  |  |  |  |  |  |  |  |  |
| **HR** |  |  |  |  |  |  |  |  |  |  |
| **RR** |  |  |  |  |  |  |  |  |  |  |
| **Temp** |  |  |  |  |  |  |  |  |  |  |

| **Time**  **(hrs)** | **0** | | **.25** | | | | **.5** | | **.75** | | | **1** | | **2** | | **3** | **4** | | **5** | | **6** | | **7** | | **8** | | | **9** |
| --- | --- | --- | --- | --- | --- | --- | --- | --- | --- | --- | --- | --- | --- | --- | --- | --- | --- | --- | --- | --- | --- | --- | --- | --- | --- | --- | --- | --- |
| **BP** |  | | |  | |  | | |  | | |  |  | | |  |  | |  | |  | |  | |  | | |  |
| **HR** |  | | |  | |  | | |  | | |  |  | | |  |  | |  | |  | |  | |  | | |  |
| **RR** |  | | |  | |  | | |  | | |  |  | | |  |  | |  | |  | |  | |  | | |  |
| **Temp** |  | | |  | |  | | |  | | |  |  | | |  |  | |  | |  | |  | |  | | |  |
| **Time**  **(hrs)** | **10** | **11** | | | **12** | | | **13** | | **14** | **15** | | | | **16** | **17** | **18** | **19** | | **20** | | **21** | | **22** | | **23** | **24** | |
| **BP** |  |  | | |  | | |  | |  |  | | | |  |  |  |  | |  | |  | |  | |  |  | |
| **HR** |  |  | | |  | | |  | |  |  | | | |  |  |  |  | |  | |  | |  | |  |  | |
| **RR** |  |  | | |  | | |  | |  |  | | | |  |  |  |  | |  | |  | |  | |  |  | |
| **Temp** |  |  | | |  | | |  | |  |  | | | |  |  |  |  | |  | |  | |  | |  |  | |

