**Appendix**

***Adverse Event Definition:***

*An adverse event (AE) is any untoward medical occurrence in a patient administered a pharmaceutical product and that does not necessarily have a causal relationship with this treatment. An adverse event can therefore be any unfavorable and unintended sign (including an abnormal laboratory finding), symptom, or disease temporally associated with the use of a medicinal product, whether or not related to the medicinal product.* *Pre-existing conditions that worsen after drug administration will be reported as adverse events. Generally an increase/ worsening of pre-existing disease status to more than 30% of baseline are reported as an adverse event. (For eg, a baseline heart rate increase from 150/ minute to more than 195/ minute, an increase of FiO2 requirement from a baseline 50% to more than 65%). This will be predefined and recorded for all infants before the start of cell therapy.*

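### The 30% during-infusion criterion cannot in practice be met by temperature, is met by SpO2 only near 62–70% (assumed baseline 88–100%), and SpO2 has no row on the printed CRF vital-sign grids

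*Combined protocol and SAP*

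**What the plan says.** Under Safety monitoring and reporting, Monitoring, the during-infusion list has two items: local site reactions, and "Any sustained change of 30% or more from baseline in vital signs (HR, RR, BP, SpO2, Temperature"). No separate limit is given for any of the five signs. Under UCBCs administration, "cell infusion will occur over one hour".

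The CRF appendix (Adverse Event Definition) gives a related convention for worsening of existing conditions: "Generally an increase/ worsening of pre-existing disease status to more than 30% of baseline are reported as an adverse event". It illustrates this with "a baseline heart rate increase from 150/ minute to more than 195/ minute" and "an increase of FiO2 requirement from a baseline 50% to more than 65" per cent. It then adds: "This will be predefined and recorded for all infants before the start of cell therapy".

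The CRF section on monitoring around the infusion prints vital-sign grids from 2 hours before the start to 48 hours after it. Every grid has the same four rows: BP, HR, RR and Temp. The pre-infusion grid ends with a blank column for acceptable limits. A separate blood-gas table has pO2 and FiO2, its own acceptable-limits row and a line headed "Cessation of acceptable limits for gas", but no SpO2.

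**The concern.** One relative threshold is applied to quantities that vary on very different relative scales. Heart rate, respiratory rate and blood pressure can plausibly shift by 30% during a reaction. Body temperature cannot, and SpO2 can do so only in profound desaturation. A listed criterion that cannot be met gives no information when it is reported as not met.

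The CRF adds a second difficulty for SpO2. A sustained change from baseline needs a recorded baseline and serial values, and the printed grids have a place for neither.

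This is a phase I safety study, and the protocol's risk section names infusion-related reactions among the risks. The item is the only numerical vital-sign criterion that the Monitoring section sets for the infusion. What is at stake is whether moderate fever, cooling or desaturation is noted as consistently as a change in heart rate or blood pressure.

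**Working it through.** **Step 1. What 30% means.** Reproduce the appendix examples with limit = baseline × 1.30:

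- Heart rate: 150 × 1.30 = 195, as stated.
- FiO2: 50 × 1.30 = 65, as stated.

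The rule is a relative change on the raw scale; for FiO2 it is not percentage points. The Monitoring item says at least 30% and the appendix says more than 30%, which makes no difference here.

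**Step 2. Signs for which the rule is usable.** From the documents' heart rate of 150 per minute the limits are 150 × 0.70 = 105 and 150 × 1.30 = 195. With assumed baselines of 50 per minute for respiratory rate and 35 mmHg for mean blood pressure, they are 35 and 65, and 24.5 and 45.5. All are workable.

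**Step 3. Temperature.** The documents give no baseline; assume 36.0–37.5 °C.

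- Required change: 0.30 × 36.0 = 10.8 °C, to 0.30 × 37.5 = 11.25 °C.
- Lower limit: 0.70 × 36.0 = 25.2 °C, to 0.70 × 37.5 = 26.25 °C.
- Upper limit: 1.30 × 36.0 = 46.8 °C, to 1.30 × 37.5 = 48.75 °C.
- A 2 °C rise is 2/37.5 = 5.3% to 2/36.0 = 5.6%.

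Fahrenheit does not help: from 98.6 °F the limits are 69.0 and 128.2 °F, or 20.6 and 53.4 °C. No plausible baseline changes the result.

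**Step 4. SpO2.** The documents give no baseline; assume 88–100%.

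- Limit for a fall: 0.70 × 88 = 61.6%, to 0.70 × 100 = 70.0%.
- A sustained fall to 75% is (88 − 75)/88 = 14.8% to (100 − 75)/100 = 25.0%, so it does not qualify.
- A baseline of 85% gives 0.70 × 85 = 59.5%; the limit drops as the baseline drops.

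**Step 5. What the printed CRF can hold.**

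| Grid | Times | SpO2 cells |
| --- | --- | --- |
| −2 to 0 h | 9 | 0 |
| 0 to 9 h | 13 | 0 |
| 10 to 24 h | 15 | 0 |
| 27 to 48 h | 8 | 0 |

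The total is 9 + 13 + 15 + 8 = 45 cells per row. As 0 h appears twice, there are 44 distinct times. Temperature has a cell at all 44 and SpO2 at none.

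Blood gases are at −1, 1, 6, 12, 24 and 48 h. None falls strictly inside the one-hour infusion, and the 1 h sample is at its end. Temperature has three readings strictly inside that hour (0.25, 0.5 and 0.75 h), or five counting both ends.

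**Step 6. Other routes for recording an event.**

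- The general adverse event definitions, in the Reporting section and the appendix, cover any unfavourable occurrence after treatment, with no size threshold for a new event.
- The CRF has a free-text area for events in the first 48 hours, and an adverse event table with respiratory, infection, systemic and other rows.
- The 48-hour criteria cover resuscitation, defined respiratory escalation and "Fluid bolus or initiation/escalation of inotropic support". Infection is also monitored over 48 hours.
- The appendix FiO2 example catches a desaturation only if oxygen is raised by more than 30% of baseline: from 21%, above 21 × 1.30 = 27.3%.
- Table 1 requires cardiorespiratory monitoring from −2 to 48 h. Adverse events are graded by CTCAE v4.0.

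These routes allow an event to be recorded. None of them prints a temperature or SpO2 limit.

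**The case against.** The strongest reply is that nothing hangs on the 30% item. The protocol lists it as something to be monitored and ties no reporting, stopping or analysis rule to it. The appendix's 30% convention concerns worsening of existing conditions, so a new fever or desaturation is an adverse event at any size and has fields on the CRF. This stands. It defeats the inference, which a reader might otherwise draw, that such events would go unrecorded.

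For temperature, a place for tighter limits already exists. The appendix says limits are set for each infant beforehand, its wording allows exceptions to 30%, and the pre-infusion grid has an acceptable-limits cell for temperature. This stands in part: the mechanism is there, but 30% is the only stated rule, and SpO2 has no row in which a limit could be written.

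A reader might also infer that SpO2 is not monitored. The documents do not support that. SpO2 is named in the Monitoring list and cardiorespiratory monitoring is scheduled. Under Data management, the medical record is the source and a REDCap database may replace paper. The gap is shown only for the printed form.

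Finally, the 62–70% figure depends on an assumed baseline. That is correct, but a lower baseline only lowers the limit.

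**Conclusion.** The concern holds as a minor defect in a stated criterion and in the printed form. Temperature cannot in practice meet the 30% rule, whatever the plausible baseline. SpO2 meets it only with a sustained fall to about 62–70%, given an assumed baseline of 88–100%. The printed vital-sign grids have no dedicated field for the SpO2 baseline or serial values.

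The consequence is limited. The primary safety outcome rests on related serious adverse events during and up to 48 hours after infusion, and on GVHD in the first three months. Neither depends on this criterion, so it would be wrong to conclude that the safety verdict is compromised. Uneven capture of non-serious infusion reactions is possible, because temperature and SpO2 are left to individual judgement or to infant-specific limits that are not stated. The documents do not show that it would occur. It would concern at most the infused infants, planned at about 20 and possibly fewer.

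**What to change.** - In the Monitoring section, keep the 30% rule for heart rate, respiratory rate and blood pressure. For temperature and SpO2, replace it with absolute limits set by the clinical team and the DSMB before the first infusion. The values are a clinical choice and none is proposed here.
- Add an SpO2 row to each printed vital-sign grid, and to the REDCap form if it lacks one. An FiO2 row would help interpretation but is optional, since FiO2 is not among the five listed signs.
- Record both limits in the existing acceptable-limits column of the pre-infusion grid.

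The cost is a short protocol wording change and one CRF row, which adds 45 time cells and one limit cell per infant. No new procedure is needed, because SpO2 is already a listed monitoring item. The downside is slightly more data entry and a few more non-serious adverse events recorded.

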At three months corrected age: General movements assessment and Hammersmith infant neurological examination

At 12 months of corrected age: Gross Motor Function Measure-66 and Infant–toddler Social and Emotional Assessment

At two years of corrected age: Bayley Scales of Infant and Toddler development-IV, and medical assessment for disability

- - - 1. Relevant laboratory tests will be performed to monitor the response and to detect any adverse events, such as GVHD

Before the infusion: Cytokine analysis, including interleukin 1b (IL-1b), IL-6, Tumour Necrosis Factor (TNF-α) and IL-10

24 h after the infusion: Cytokine analysis, full blood examination (FBE), chimerism assessment and LFTs

4 day, 1 week and 1 month chimerism assessment

1 week, 1 month and 3 months post-transfusion: FBE and LFTs

Chimerism assessment will be repeated at 3 months if there are detectable donor cells at 1 month testing (optional assessment)

Lymphocyte subset analysis will also be performed if white cell count is low, which is consistent with GVHD

- - 1. **Data Safety Monitoring Board (DSMB)**: A DSMB consisting of a neonatologist, and paediatric neurologist or cell therapist or haemato-oncologist will be established to review all the adverse events. All serious events will be reported to DSMB within 7 days of occurrence.
       - 1. *Interim analysis:* DSMB will be requested to conduct an interim analysis following the enrolment of five patients in each group to assess the feasibility and adverse events. DSMB and HREC will also review whenever there is a serious event to ensure it is safe to continue the trial.
         2. *Criteria for premature termination of trial*: DSMB and HREC will be consulted for an independent review of trial conduct, progress and any serious events related to cell therapy, which will further determine whether the trial requires premature termination. No predetermined interim analysis will be conducted. The analysis will only be conducted after at least 10 infants have been recruited in each stratum.
    2. Reporting:
       1. Any events occurring after the allogeneic UCBC therapy will be reported to the relevant parties. Events will be categorised as per the National Health and Medical Research Council 2016 recommendation^31^ and report any related or unrelated events

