**INTERVENTION (Examine**, **blood** for cytokines, **administer UCBCs)**

**Blood** for cytokines (24 h) & assess for side effects (up to 48 h)

**Blood** for chimerism (4d)

**Blood** for FBE, LFTs and chimerism (1w, 1m)

**GVHD assessment** at 2 m

**Blood** (FBE/LFTs), & **GVHD assessment** (3m)(***SAFETY***)

**MRI** at TEA

**Assessments: Neurological** (3, 12, 24 m) and **GVHD** (6, 9, 12, 18, 24m)

**Table 1**: Safety, adverse events, and neurological outcome monitoring

| Timeline | Cardiorespiratory monitoring | Infection monitoring | Physical examination | Cytokine analysis | FBE*, chimerism assessment and LFT | Neurodevelopmental assessment | Neuroimaging |
| --- | --- | --- | --- | --- | --- | --- | --- |
| -2 to 0 h | √ | √ | √ | √ |  |  |  |
| 0 to 48 h | √ | √ |  |  |  |  |  |
| 24 h |  |  | √ | √ | √ |  |  |
| 4 d |  |  |  |  | √ (Chimerism only) |  |  |
| 7 d |  |  | √ |  | √ |  |  |
| 1 m |  |  | √ |  | √ |  |  |
| 2 m |  |  | √ |  |  |  |  |
| 3 m |  |  | √ |  | √ (Chimersim is optional) | √ (TEA) | √ (MRI at TEA) |
| 6 m |  |  | √ |  |  | √ (3 m CA) |  |
| 9 m |  |  | √ |  |  |  |  |
| 12 m |  |  | √ |  |  | √ (12 m CA) |  |
| 18 m |  |  | √ |  |  |  |  |
| 24 m |  |  | √ |  |  | √ (24 m CA) |  |

**Note**: CA, corrected age; FBE, full blood examination (*-lymphocyte subset analysis for patients with abnormal FBE consistent with GVHD, and chimerism analysis will be repeated at 3, 6 or 12 months if there are detectable donor cells at 1 and/or 3 months testing); LFT, liver function test; MRI, magnetic resonance imaging; TEA, term equivalent age

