**Details of care on day of UCBCs**

| **Date** | **Day of life** | | **Corrected gestation** | |
| --- | --- | --- | --- | --- |
| **Current Weight (date)** | | | | |
| **Current respiratory support** | | **Settings** | | **FiO2** |
| **Last cranial USS (date)** | | | | |
| **Last Echocardiogram (date)** | | | | |
| **Last serum chemistry (date)**  **FBE (date)** | | | | |
| **Medications** | | | | |
| **Feeds** | | | | |

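### No liver function test is scheduled before infusion, so an abnormality at the 24-hour test may not be classifiable as new, worsened or pre-existing

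*Combined protocol and SAP*

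**What the plan says.** Protocol, *Safety monitoring and reporting*, laboratory tests. The tests are meant to follow the response and pick up adverse events, with GVHD as the named example. The pre-infusion entry is "Before the infusion: Cytokine analysis, including interleukin 1b (IL-1b), IL-6", completed by TNF-α and IL-10. The next entry is "24 h after the infusion: Cytokine analysis, full blood examination (FBE), chimerism assessment and LFTs", and the later ones are "1 week, 1 month and 3 months post-transfusion: FBE and LFTs".

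The same section lists among the acute GVHD features "Liver involvement: jaundice, conjugated hyperbilirubinemia, and abnormal liver function tests (LFTs"), with no threshold and no reference to change from baseline.

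Table 1 has a column headed "FBE*, chimerism assessment and LFT". It is blank in the -2 to 0 h row and ticked at 24 h, 7 days, 1 month and 3 months.

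Figure 1 shows blood for HLA typing and then for cytokines before the cells. After them it shows blood "for cytokines (24 h) & assess for side effects (up to 48 h"), then "for FBE, LFTs and chimerism (1w, 1m"), then FBE and LFTs at 3 months.

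The case report form (CRF) page *Details of care on day of UCBCs* has a field "Last serum chemistry (date") and a dated FBE field. The CRF grid *GVHD Assessment and bloods* has a pre-infusion row in which chimerism is marked not applicable and the laboratory and liver cells are open.

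The CRF appendix, *Adverse Event Definition*, counts an abnormal laboratory finding as a possible adverse event. As a general guide it treats worsening by more than 30% over baseline as reportable, and it says this will be set and recorded for every infant before the cells are given.

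**The concern.** In a single-arm trial, an infant's own pre-infusion value is the only comparator for a later laboratory result. The plan uses LFTs to look for GVHD and has an adverse event rule that depends on a baseline, but no scheduled test supplies that baseline for LFTs. A liver abnormality that was present before infusion could be attributed to the cells, or a real early change could be put down to the infant's prior state. A baseline that was not taken cannot be recovered afterwards.

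FBE has the same gap but matters less. It has its own dated CRF field, and a low white cell count leads only to lymphocyte subset analysis.

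**Working it through.** The plan states no figure to reproduce, so the check sets the sources side by side.

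**1. Scheduled LFTs**

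| Source | Before infusion | 24 h | 1 week | 1 month | 3 months | Total after |
|---|---|---|---|---|---|---|
| Protocol text | no | yes | yes | yes | yes | 4 |
| Table 1 | no | yes | yes | yes | yes | 4 |
| Figure 1 | no | not shown | yes | yes | yes | 3 |

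All three agree on 0 before infusion. The text and Table 1 agree on 24 h, so that is taken as the schedule; the flow chart omits it.

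**2. Does the CRF supply the missing value?** Only in part.
- The infusion-day page asks for the last serum chemistry. It does not name LFTs and sets no limit on the age of the result.
- The open pre-infusion laboratory cell in the GVHD grid can hold a result but does not order one. The same cell is open at 2, 6, 9, 12, 18 and 24 months, when no LFT is scheduled.

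**3. Does the 30% rule supply it?** The appendix examples are heart rate (150 × 1.30 = 195) and FiO2 (50% × 1.30 = 65%). Both need a measured starting value. LFTs are not mentioned, and no scheduled test gives their starting value.

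**4. What can be classified in an infant with no recent routine LFT** (text and Table 1 schedule)
- Normal at 24 h, abnormal later: new since 24 h, so classifiable.
- Abnormal at 24 h, whether or not it persists: could be pre-existing, worsened or new, so not classifiable.
- Abnormal at 24 h and higher later: the further rise is visible, but the origin of the 24 h value is not.

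If a team worked from Figure 1 alone, the same ambiguity would move from 24 h to 1 week.

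**5. Cost of a baseline.** With the planned 20 infants all infused (the *Sample size* section says the number may be smaller):
- planned post-infusion LFTs: 20 × 4 = 80;
- added samples: at most 20 × 1 = 20, and 0 if every infant has a routine result in the window;
- relative increase: 20 / 80 = 25% at most.

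These counts measure the cost of the fix, not the harm from the gap.

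**6. Scale, on an assumption.** The documents do not say how often LFTs are already abnormal at infusion. If each infant independently has probability p, the chance of at least one such infant among n is 1 − (1 − p)^n.

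| Assumed p | n = 10 | n = 20 |
|---|---|---|
| 5% | 40% | 64% |
| 10% | 65% | 88% |
| 20% | 89% | 99% |

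This is not the frequency of unclassifiable results. Some of these infants would have a usable routine result, which lowers it. Abnormalities that truly arise in the first 24 h would also be unclassifiable in infants without one, which raises it.

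**The case against.** The strongest reply is that the plan already has most of a baseline. The appendix promises that reference values are recorded before the cells are given. The GVHD grid rules out pre-infusion chimerism but leaves the laboratory and liver cells open, which suggests that a baseline entry was intended. The infusion-day page asks for the last chemistry with its date. The pre-infusion examination could show jaundice, and chimerism and DSMB review add further evidence. All of this stands, and it narrows the gap. It does not close it: none of these items orders an LFT or limits how old a result may be, and an examination cannot show a purely biochemical abnormality. A recent routine LFT cannot be assumed either. Infusion may take place up to three months of life, in clinically stable infants, in the neonatal unit or the clinical trials facility.

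A second reply is that the 24 h LFT serves as a within-infant reference. That is right for the 1-week, 1-month and 3-month results. It leaves only the 24 h result itself and anything already abnormal then.

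A reader might go further and infer that the primary safety criterion cannot be assessed, because the Unlikely, Possible and Probable causality definitions all turn on timing. The documents do not support this. In the primary safety outcome, relatedness qualifies serious adverse events up to 48 h after infusion. Absence of GVHD is a separate requirement with no relatedness test. Only the 24 h LFT falls within the 48 h window, and it would have to form part of a serious event to count there. Abnormal LFTs alone are not stated to make a GVHD case, and the causality definitions also weigh the infant's clinical state.

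**Conclusion.** The point holds in a limited form. The text, Table 1 and Figure 1 schedule no LFT or FBE before infusion, although abnormal LFTs are a listed acute GVHD feature and the adverse event rule needs a pre-infusion value. In an infant without a recent routine LFT, an abnormality found at 24 h, or already present then and persisting, cannot be classed as new, worsened or pre-existing. An abnormality that follows a normal 24 h result can be identified as new.

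The effect is on attribution of individual liver findings that feed the GVHD assessment and adverse event reporting. It does not directly alter the primary criterion. Its frequency cannot be computed, because the documents give neither the rate of abnormal LFTs at infusion nor the share of infants with a recent routine result. The conclusion takes the text and Table 1 as the operative schedule. This is a cheap improvement, worth making before infants are infused.

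**What to change.** - Add LFTs with conjugated bilirubin, and FBE, to the pre-infusion line of the laboratory schedule, the -2 to 0 h row of Table 1 and the intervention box of Figure 1, drawn with the planned cytokine sample. Alternatively, accept a routine result from a stated window, for example 72 h before infusion.
- Show the 24 h FBE and LFTs in Figure 1, so that it matches the text and Table 1.
- Name LFTs on the infusion-day CRF page, and enter values and dates in the pre-infusion row of the GVHD grid.
- Report post-infusion LFT and FBE abnormalities per infant as new or worsened against that baseline, and state whether the 30% guide applies to laboratory values.

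The cost is one line of text, a table tick, a figure edit and a CRF field with a window. The downside is a small extra blood volume, only in infants without a recent routine result. It should need no separate draw if the planned pre-infusion sample is large enough; the documents give no blood volumes, so this needs confirming.
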